### Blinding

Due to the nature of the acupuncture and moxibustion interventions, neither participants nor care providers can be blinded to allocation and treatment stages, but are strongly inculcated not to disclose the allocation status of the participant at the follow-up assessments. The outcome assessment will be conducted by outcome assessors blind to the treatment allocation. In the stage of data analyses, an employee outside the research team will feed data into the computer in separate datasheets so that the data analysts can analyze the data without having access to information about the allocation.

To maintain the overall quality and legitimacy of the clinical trial, code breaks should occur only in exceptional circumstances when knowledge of the actual treatment is absolutely essential for further management of the patient. Investigators, including the outcome assessors and data analysts blind to treatment allocation, are encouraged to discuss with the medical advisor physicians if they believe that unblinding is necessary. The investigator is encouraged to maintain the blind as far as possible. The actual allocation must *not* be disclosed to the patient and/or other study personnel. There should not be any written or verbal disclosure of the code in any of the corresponding patient documents. The investigator must report all code breaks (with reason) as they occur on the corresponding Case Report Form page. Unblinding should not necessarily be a reason for study drug discontinuation.

### Data collection methods

The method of outcome data collection has been listed in previous parts. In order to ensure the data quality, each site’s personnel involved in this study will be trained to master the data collection requirements; the data to be collected and the procedures to be conducted at each visit will be reviewed in detail.

### Participant retention

In order to promote participant retention, once a patient is enrolled or randomized, the study sites will make every reasonable effort to follow the patient for the entire study period. In detail, study investigators and staff will:Maintain participants’ interests by materials and phone callsProvide periodic communications via materials and talks to inform the participants of our acknowledgement for their supportBe as flexible as possible with the study schedule in resolving time conflicts with participants’ work and life

### Participant withdrawal

Participants will possibly withdraw from the study due to any reason at any time. The study investigators may also withdraw participants from the study with the purpose of protecting them and/or if they are unwilling to follow the study procedures. Once a withdrawal happens, it should be recorded by the steering committee and the data management team.

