**Fig. 2 Fig2:**
[figure not shown]
Treatment regimen flowchart. This figure demonstrates the treatment regimen and flowchart for intervention of warm needling and medicinal cake-separated moxibustionSimvastatinDosage: simvastatin (10 mg/day)AdministrationAll simvastatin tablets will be stored in the central pharmacy and assigned to each investigator site by a qualified staff. The drug will be administered orally to subjects at the investigator site by a physician or a nurse in accordance with instructions in the medication guidesSchedule: 7 days per week for 12 weeksDosage adjustment:there will be no dose adjustments in this study. If, in the opinion of the investigator, a subject is unable to tolerate a specific dose of simvastatin and requires dosage adjustment, that subject will discontinue simvastatin but will continue to return for all other study procedures and measurements until the end of the study

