### Discontinuity of intervention

Subjects in the study are able to withdraw from the study at any time, either partially or entirely.

When a subject fully consents to withdrawal from the study, the subject will no longer receive the investigational treatment and will have the right to discontinue any further involvement in the study, including any format of follow-up. Below is a list of reasons for discontinuing intervention:Withdrawal of full consent from subjectSubject requests the ending of investigational interventionAdministrative decision by the principal investigatorUnanimous decision by the principal investigator/physicianPregnancy in a female subjectAdverse event (e.g., serious adverse event related to the intervention)

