#### Statistical analysis plan

The primary analysis set for the primary endpoint is the FAS. It is to use the repeated measures, linear mixed-effects model, including terms for treatment group, stratification factor, baseline LDL-C, scheduled visit and the interaction of treatment with scheduled visit. Missing values will not be imputed when the repeated measures, linear mixed-effects model is used.

We will use the chi-squared test for binary outcomes, and the *t* test for continuous outcomes. For subgroup analyses, we will use regression methods with appropriate interaction terms (respective subgroup treatment group). Multivariable analyses will be based on logistic regression for binary outcomes and linear regression for continuous outcomes. We will examine the residual to assess model assumptions and goodness-of-fit. For timed endpoints, such as mortality, we will use the Kaplan-Meier survival analysis followed by the multivariable Cox proportional hazards model for adjusting for baseline variables. We will calculate Relative Risk (RR) and RR Reductions (RRR) with corresponding 95% confidence intervals to compare dichotomous variables, and difference in means will be used for additional analysis of continuous variables. *P* values will be reported to four decimal places with *P* values < 0.05 reported as *P* < 0.05. Up-to-date versions of R (R Foundation) will be used to conduct analyses. For all tests, we will use two-sided *P* values with alpha no greater than 0.05 level of significance. We will use the Bonferroni method to appropriately adjust the overall level of significance for multiple primary outcomes, and secondary outcomes.

In investigation of the robustness of the analysis results, the primary analysis will be repeated using the CAS. In addition, parametric analysis of covariance (ANCOVA) and appropriate nonparametric methods will be used on the FAS, in which missing data will be imputed using the last-observation-carried-forward (LOCF) approach. The primary analysis will also be repeated for subgroups of interest.

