#### Adverse events and participant withdrawal

The investigator will use his/her clinical judgment to determine whether a subject should be removed from the study due to adverse events. The subject or their legal representatives also have the full right to withdraw from the treatment due to an adverse event or concerns for an adverse events. However, the investigator will encourage the subjects to undergo at least an end of the study assessment.

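### Investigators who know the allocation may remove participants from the study for not following procedures, while continued LDL-C measurement after stopping is required only for simvastatin intolerance

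*Protocol article*

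**What the plan says.** The protocol article deals with stopping and leaving in five places.

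- **Participant withdrawal.** Investigators "may also withdraw participants from the study with the purpose of protecting them and/or if they are unwilling to follow the study procedures". The wording covers participants in both arms and refers to leaving the study. It does not ask for any later LDL-C measurement.
- **Interventions, simvastatin dosage adjustment (after Fig. 2).** If "a subject is unable to tolerate a specific dose of simvastatin and requires dosage adjustment", then "that subject will discontinue simvastatin but will continue to return for all other study procedures and measurements until the end of the study". No matching sentence is written for a subject who stops acupuncture and moxibustion.
- **Discontinuity of intervention.** "Subjects in the study are able to withdraw from the study at any time, either partially or entirely". Full withdrawal of consent ends follow-up. The section does not say which measurements continue after a partial withdrawal.
- **Participant retention.** For everyone who has entered the trial, in both arms, it promises that "the study sites will make every reasonable effort to follow the patient for the entire study period".
- **Adverse events and participant withdrawal.** When a subject leaves because of an adverse event, "the investigator will encourage the subjects to undergo at least an end of the study assessment".

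On the analysis, the Statistical analysis plan section makes the full analysis set (FAS) primary, with a repeated-measures mixed model: "Missing values will not be imputed when the repeated measures, linear mixed-effects model is used". The robustness checks are a repeat in the completer set (CAS), and ANCOVA and nonparametric methods on the FAS in which "missing data will be imputed using the last-observation-carried-forward (LOCF) approach".

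**The concern.** Whether LDL-C is measured after a subject stops treatment is a conduct rule. A sample never drawn cannot be recovered by any later analysis. Here the article gives investigators discretion to end measurement for a reason tied directly to adherence. Under Blinding, care providers know the allocation, and the limitations in the Discussion already expect more drop-off and cross-over, with possible selection bias, because patients know their arm.

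The primary mixed model uses only observed values and relies on the missing ones being explained by what is in the model. Adherence is not among the listed terms. If poor adherers leave and adherers stay, an arm's mean can look better than it would under full follow-up. In a noninferiority comparison the effect on the conclusion depends on which arm loses such subjects. The only written duty to keep measuring after stopping sits in the control arm, so the two arms are not protected alike.

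**Working it through.** **1. The plan's own figure.** The Sample size section gives an effect of 0.343 on absolute LDL-C change, SD 0.7 and power 0.80. With two-sided alpha 0.05:

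n per group = 2 × [0.7 × (1.960 + 0.842) / 0.343]² = 65.4.

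This agrees with the stated figure of about 65 (power at 65 is 0.798). The corresponding standard error of the difference is 0.7 × √(2/65) = 0.123. The section gives no unit for 0.343 and does not call it a margin. It also assumes that 90% remain, a 10% allowance for all missing observations and losses, not a rate of non-adherence.

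**2. What happens to a subject's later LDL-C, by route.**

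| Route | Arm | Later LDL-C |
|---|---|---|
| Cannot tolerate simvastatin | Control | Required to study end |
| Partial withdrawal | Either | Not specified |
| Leaves after an adverse event | Either | Final assessment encouraged |
| Removed by investigator for not following procedures | Either | Not asked for |
| Full withdrawal of consent | Either | Ends |

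**3. What the analyses do with it.** The FAS keeps a removed subject who had at least one treatment, but only with the values already collected. The CAS drops everyone who did not complete the intervention, in both arms, including the simvastatin stoppers who were kept for measurement. Carrying the last value forward can put a week-6 value obtained on treatment in place of week 12. None of these supplies the missing off-treatment value.

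**4. Direction and size, on assumed inputs.** Let E_a and E_s be the on-treatment falls in LDL-C, q_a and q_s the shares that stop, and let stoppers show no change. Write the difference as acupuncture minus simvastatin, so that positive means acupuncture is worse.

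- Full follow-up: (1 − q_s)E_s − (1 − q_a)E_a.
- Only acupuncture stoppers removed: (1 − q_s)E_s − E_a. Shift = −q_a E_a, toward noninferiority.
- Stoppers removed in both arms: E_s − E_a. Shift = q_s E_s − q_a E_a.
- Only simvastatin stoppers removed: E_s − (1 − q_a)E_a. Shift = +q_s E_s, against noninferiority.

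With 10% stopping:

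- Acupuncture arm only, E_a = 0.5, 0.7 or 1.0: shift of 0.05, 0.07 or 0.10 toward noninferiority. Against the standard error, 0.05/0.123 = 0.41 and 0.10/0.123 = 0.81.
- Both arms, E_a = E_s = 1.0: 0.10 − 0.10 = 0.
- Both arms, E_s = 1.0 and E_a = 0.657: 0.100 − 0.066 = 0.034 against noninferiority.

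These are complete-case calculations on absolute change. The primary endpoint is percentage change, and the mixed model would also use week-6 values where they exist, so the actual shift may be smaller. They are not converted into a type I error because the article states no margin for this endpoint.

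**The case against.** A reader might infer that simvastatin stoppers are kept while non-adherent acupuncture subjects are removed, so that the trial is tilted toward noninferiority. The documents do not support this. The Participant withdrawal rule covers both arms. The simvastatin sentence is a dose-adjustment clause that retains only intolerance stoppers, not those who leave for preference or poor adherence. Step 4 shows that the shift can be zero or run the other way. This part of the objection stands in full.

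A reader might also see a flat contradiction with Participant retention. That section promises best efforts, which can coexist with a withdrawal clause. The two need reconciling, but neither falsifies the other.

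Three further points carry some weight. Appendix 2 (Lipid Measurements) blinds investigators, subjects and the study team to lipid values after randomization, so subjects cannot be removed on their observed response. Dropout related to adherence is not automatically missing not at random, because week-6 LDL-C may carry part of the information. The article condenses a fuller protocol, where rules on follow-up after discontinuation may be written out.

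None of these disposes of the point. Blinding to lipids does not stop selection on adherence. A subject removed before week 6 contributes no post-baseline value. The difficulty is also a rule that the article does state, ending study participation for not following procedures, rather than an omission.

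**Conclusion.** The point holds as a badly fixed conduct rule. In either arm, investigators who know the allocation may end outcome measurement for a reason tied to adherence; only simvastatin intolerance carries a duty to keep measuring; and none of the planned analyses restores what is lost.

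The consequence is a risk, not a demonstrated bias. Unequal use of the rule between arms could bias the comparison, possibly toward noninferiority. The article gives no stopping rates by arm, no expected on-treatment falls and no noninferiority margin, so neither direction nor size can be established. The shift of 0.05 to 0.10 is an illustration that rests on three assumptions: 10% removed from the acupuncture arm alone, no LDL-C change in those removed, and a fall of 0.5 to 1.0 in the others. It should not be read as an estimate. The change is worth making because it is cheap and must be in place before the samples are missed.

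**What to change.** Reconcile the simvastatin dosage-adjustment text, Discontinuity of intervention, Participant retention, Participant withdrawal, and Adverse events and participant withdrawal, so that all five state one rule for both arms. Stopping or not following the assigned intervention does not end the scheduled week-6, 12 and 16 LDL-C and safety measurements; only the subject's withdrawal of consent to follow-up does. Under Participant withdrawal, unwillingness to follow procedures would then end the intervention and not study participation. Under Discontinuity of intervention, partial withdrawal should be described as continuing these measurements.

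This concerns outcome measurement only. The reasons for stopping treatment stay as the sponsor decides.

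The cost is protocol wording and a few more retention contacts. The visits are already scheduled.

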### Data management

#### Data forms and data entry

In this study, all data will be entered electronically. Original data along with the data collection form will be archived at the participating sites. Once a form has been filled out, the participating site staff will copy the form and send it to data management team for electronic re-entry.

Participant files will be stored by participation number. The storage location should be secured and accessible. The files will be kept in storage for 5 years after the study.

#### Data transmission and editing

Data transmission refers to the transmission of data from the original data form to computers used by the data management team. Data entry staff will carefully check whether the transmission is correct at the time of data entry. Data editing, either modification on single record or on multiple records, will be documented, along with the reason of the editing.

#### Data discrepancy reports and solutions

Errors may be detected by data analysts, including missing data error, or other specific errors in the data. The analyst should summarize the error and report to the data manager. The data manager who receives the data discrepancy reports will forward the specific problem to the data management staff in the participating site, retrieve the original data forms, and check whether there is an inconsistency.

There are several solutions for data discrepancy. If the data in the database is inconsistent with the original form, a primary choice is to correct the record in the database. Other alternative choices include missing data imputation techniques, data correction by checking other sources, and modifying the original data. The discrepancy reports and solutions should be documented for future reference.

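### The data-management rules allow missing values to be imputed and original data to be modified, and nothing keeps such values out of a primary analysis that is meant to be free of imputation

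*Protocol article*

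**What the plan says.** All references are to the protocol article.

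**Data discrepancy reports and solutions.** Missing data are classed as a kind of error: "Errors may be detected by data analysts, including missing data error, or other specific errors in the data". The preferred remedy is conventional: "If the data in the database is inconsistent with the original form, a primary choice is to correct the record in the database". The next sentence widens the choice: "Other alternative choices include missing data imputation techniques, data correction by checking other sources, and modifying the original data". The section ends with a record-keeping rule: "The discrepancy reports and solutions should be documented for future reference".

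**Neighbouring data-management sections.** Data transmission and editing requires that "Data editing, either modification on single record or on multiple records, will be documented, along with the reason of the editing". Data forms and data entry says that "Original data along with the data collection form will be archived at the participating sites".

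**Statistical analysis plan (the section of that name).** For the primary analysis on the full analysis set: "Missing values will not be imputed when the repeated measures, linear mixed-effects model is used". Imputation appears only in the robustness work, where ANCOVA and nonparametric methods are run on the full analysis set and "missing data will be imputed using the last-observation-carried-forward (LOCF) approach".

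**Dataset analysis.** The completer set (CAS) requires a nonmissing week-12 LDL-C. The durability set (EDAS) requires nonmissing week-6 and week-12 LDL-C.

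**The concern.** Two parts of the same document give different rules for a missing value. The analysis section leaves it missing and lets the mixed model handle it. The data-management section lets it be filled before the analyst sees it. If both are followed, the no-imputation rule is kept in form only: the model imputes nothing because the gap has already been closed.

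What is at stake is the error rate of the primary noninferiority comparison and the independence of the check on it. Singly imputed values treated as measurements add apparent sample size without information, so the standard error is too small. Because membership of the CAS and EDAS turns on nonmissing LDL-C, the same filled value could move a subject into the set used to test robustness.

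Permission to modify the original data is a second, separate problem. When database and source disagree, the source is the reference. A rule that lets the reference be altered to settle the disagreement removes the fixed point against which the database is checked.

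**Working it through.** **1. The texts side by side**

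| Question | Data discrepancy section | Statistical analysis plan section |
|---|---|---|
| Is a missing value something to be resolved? | Yes, listed among errors | No, left missing in the primary model |
| May it be imputed? | Yes, as an alternative solution | Not for the mixed model; LOCF in sensitivity analyses only |
| Which variables? | No limit stated | LDL-C for the primary endpoint |
| Is a filled value flagged, kept apart or reset to missing before analysis? | Not stated; solutions are documented | Not stated |

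The last row decides the matter. Documentation makes a filled value traceable afterwards, but no sentence keeps it out of the analysis file.

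**2. The plan's own figures**

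The plan gives no figure for the effect of data-management imputation. The one input used below is the retention assumption in the Sample size section: 90% remain, so 10% are lost. The sample size in that section is background and is not in dispute. With an effect of 0.343, SD 0.7, two-sided 5% and 80% power:

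n = 2 × (1.96 + 0.8416)² × (0.7/0.343)² = 65.4 per group, that is 66 after rounding up, against the stated approximate 65.

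**3. Size of the effect if gaps were filled (illustration)**

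Assumptions that are not in the protocol: a single-visit comparison of means, equal loss in both arms, and each gap filled with its own arm's mean and then counted as observed. Let N be the number per arm and s the SD.

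- Correct SE of an arm mean, from the 0.9N observed values: s / √(0.9N).
- After filling, the sample variance falls to about 0.9s², because the filled values contribute no spread, and it is divided by N: SE = √(0.9s²/N).
- Ratio: √(0.9 × 0.9) = 0.90, so the SE is about 10% too small.
- Effective critical value: 1.96 × 0.90 = 1.764.
- Actual two-sided error: 2 × (1 − Φ(1.764)) = 0.078, against a nominal 0.05.

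**4. Sensitivity to the amount of filling**

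In general the ratio is (number observed)/(number analysed). If only half of the 10% were filled and the rest left missing, the ratio is 0.90/0.95 = 0.947, the effective critical value is 1.96 × 0.947 = 1.857, and the two-sided error is 2 × (1 − Φ(1.857)) = 0.063. With no filling it returns to 0.05. The range over this assumption is therefore 5% to 7.8%.

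**5. Cross-check by simulation**

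The set-up was 70 per arm with 7 missing in each, a one-sided nominal 2.5% test, and the true difference placed at a stand-in margin of 0.343 (the protocol's effect size, used here only as a margin). False noninferiority was about 2.6% on the observed data and 4.0% after own-arm mean filling. Half of 7.8% is 3.9%, so the formula and the simulation agree.

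**The case against.** The strongest reply is that the discrepancy section is a generic list covering any variable, while the analysis section gives a specific rule for the primary model, and the specific rule should govern. On that reading the mention of imputation techniques merely anticipates the LOCF analyses. This is a possible reading, and it is why the point is put as something the text permits. It does not dispose of the point, because the two rules act at different stages. A rule about what is done when the model is used does not reach a value already filled upstream.

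The illustration is also open to challenge. The section does not name mean filling, the planned loss need not all be filled, and the primary analysis is a repeated-measures model. All of that stands: the 7.8% shows the mechanism and does not forecast this trial's error rate.

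A reader might infer several stronger things that the documents do not support:

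- *That the plan intends to impute LDL-C.* It says nothing of the kind.
- *That the audit trail would be destroyed.* Edits and their reasons must be documented, discrepancy solutions likewise, and original data are archived at the sites.
- *That site staff who know the allocation would choose the values.* The section has analysts report errors and the data manager forward them to site data-management staff. It does not say who would choose an imputed value. The Blinding section names participants and care providers as unblinded, and Lipid Measurements in Appendix 2 keeps investigators and the study team blinded to post-randomization lipid results.
- *That LOCF is the only alternative handling of missing data and must be replaced.* The primary analysis is also repeated on the CAS, which treats missing week-12 values differently. The choice of LOCF as one sensitivity analysis is a separate matter and no part of this point.

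**Conclusion.** The inconsistency is real and lies in stated text, so it cannot be put down to detail left to a fuller protocol or a separate SAP. The discrepancy section permits imputation and modification of original data without limit, the primary analysis excludes imputation, and nothing connects the two rules. Filled values could therefore enter the primary model as observed and could alter CAS and EDAS membership.

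The size depends on how far the permission is used, which the document does not say. Under the assumptions in the working, the upper end at the planned 10% loss is a standard error about 10% too small and a two-sided error of about 7.8% instead of 5%; with no filling there is no effect. The conclusion rests on the conflict of wording and not on these figures. It is worth correcting because the permission bears on the primary noninferiority test and is nearly free to remove.

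**What to change.** In Data discrepancy reports and solutions:

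1. From the sentence "Other alternative choices include missing data imputation techniques, data correction by checking other sources, and modifying the original data", delete the first option (imputation) and the third (modification of original data). Keep correction from other sources only where the other source is itself verified.
2. State that the database is corrected only to agree with verified source.
3. State that any correction to a source record is a dated, attributable addition that leaves the first entry legible.
4. State that a value that cannot be retrieved stays missing in the database.
5. Add a cross-reference confining imputation to the sensitivity analyses named in the Statistical analysis plan section.

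The cost is a few lines of data-management wording. No change to the sample size, the primary model or the planned sensitivity analyses is needed. If any discrepancies have already been settled by imputation or by altering an original record, the discrepancy log required by the protocol should allow those values to be identified and reset to missing or to the original entry before the primary analysis.
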